**PROJECT OVERVIEW**

The study will be performed in two parts:

1. The demographic characteristics for women with a hypertensive disorder of pregnancy (i.e., chronic hypertension, gestational hypertension, or preeclampsia) and their infants will be described and compared based on pregnancy exposure to labetalol or nifedipine.
2. By applying a causal framework to the statistical analysis of our observational data, we will determine the *causal effect* of exposure to nifedipine for the management of hypertensive disorders of pregnancy, compared with exposure to labetalol, on maternal and perinatal adverse outcomes. This approach will be used to mimic the conduct of a target randomized controlled trial seeking to recruit pregnant women who require treatment with antihypertensives.
   1. **P**opulation – All women who gave birth in Victoria between 2009 – 2020 and whose pregnancies were affected by hypertensive disorders.
   2. **I**ntervention – Exposure to nifedipine from 11 weeks’ gestation.
   3. **C**ontrol – Exposure to labetalol from 11 weeks’ gestation.
   4. **O**utcome – Adverse maternal and neonatal outcomes (see *Outcome Definitions* below).
   5. **T**iming – From 11 weeks’ gestation until 28 days postpartum.

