| **(D) Follow-up period** | From 11 weeks’ gestation until 28 days post-birth. | From 11 weeks’ gestation until 28 days post-birth. |
| **(E) Outcomes** | **Primary Maternal**  Severe hypertension (systolic blood pressure ≥160mmHg).  **Primary Neonatal**  Composite of stillbirth, neonatal death (until 28 days post-birth), and NICU admission requiring separation of infant and mother (until 28 days post-birth).  **Secondary Maternal**  *Note: Variables denoted with a * are reported with treatment effect and 95% CI, all others are exploratory only and described with summary statistics*.   - Mean antenatal systolic blood pressure* - New diagnosis of preeclampsia* - Severe maternal morbidity (fullPIERS consensus definition)* - Discontinuation of allocated antihypertensive* - Undesirable effects of allocated antihypertensive* - Maternal death* - Indicated birth (induction of PROM)* - Mean antenatal diastolic blood pressure - Proportion of days with antenatal systolic blood pressure ≥140mmHg - Proportion of days with antenatal diastolic blood pressure ≥90mmHg - Diagnosis of eclampsia - Diagnosis of HELLP syndrome - Placental abruption - Components of severe maternal morbidity - Maternal stroke - Prescription of additional antihypertensive drugs - Prescription of alternative antihypertensive drugs - Time from randomization to first discontinuation of allocated antihypertensive - Total number of antenatal hospital inpatient days - Treatment satisfaction - Beliefs about allocated antihypertensive drug - Adherence to allocated antihypertensive drug - Mode of onset of birth   **Secondary Neonatal**  *Note: Variables denoted with a * are reported with treatment effect and 95% CI, all others are exploratory only and described with summary statistics*.   - Major congenital anomaly (as defined by EURO-CAT)* - Birthweight centile* - Need for treatment for neonatal hypoglycemia* - Neonatal unit admission (separation of baby from mother)* - Mode of birth* - Gestational age at birth* - Fetal loss <24^+0^ weeks’ gestation - Fetal loss ≥24^+0^ weeks’ gestation (stillbirth) - Known early neonatal death (up to 7 days post-birth) - Known late neonatal death (7-28 days post-birth) - Principal recorded indication for neonatal unit admission - Length of stay in neonatal unit (and level of care) - Indication for mode of birth - Preterm birth (<37 completed weeks) - Preterm birth (<32 completed weeks) - Birthweight - Birthweight SGA (<10^th^ centile) - Umbilical arterial pH<7 at birth - Apgar score 5min post-delivery - Need for additional resuscitation at birth - Need for respiratory support - Type of respiratory support needed - Type of treatment for hypoglycemia - Lowest blood glucose measurement within 48 hours post-birth - Intracranial hemorrhage - Neonatal seizures - Necrotizing enterocolitis | **Primary Maternal**  Our primary outcome will be a composite of severe maternal morbidity determined by an expert panel, comprising:   - Maternal mortality (all cause) - Eclampsia - HELLP syndrome - Stroke - Cortical blindness - Retinal detachment - Pulmonary oedema - Placental abruption - Liver rupture - Need for dialysis - Need for extracorporeal membrane oxygenation (ECMO)   *Note: We do not have reliable ascertainment of ICU/HDU admission data. By instead including only severe morbidities which can reasonably be attributed to hypertensive disorders, we will provide a more accurate picture of the effect of disease-modifying drugs.*  **Primary Perinatal**  Our primary perinatal outcome will be a composite outcome determined by expert consensus. This will comprise.   - Stillbirth (fetal death ≥20 weeks’ gestation) - Neonatal death (death within 28 days of birth) - Severe neonatal morbidity, including:   - Bacterial sepsis   - Birthweight < 3^rd^ centile   - Cardiac arrest   - Hypoxic-ischemic encephalopathy (HIE)   - Intracranial hemorrhage   - Necrotizing enterocolitis   - Neonatal asphyxia   - Neonatal seizures   - Requirement for intubation or mechanical ventilation   - Requirement for resuscitation (mechanical or non-mechanical)   *Note: We do not have reliable ascertainment of NICU admission data. Many infants who are born following hypertensive pregnancies will be admitted to NICU without any other severe morbidities. By instead including only diagnosed severe morbidities, we will provide a more accurate picture of the effect of disease-modifying drugs.*  **Secondary Maternal**  *Note: Variables denoted with a * are reported with treatment effect and 95% CI, all others are exploratory only and described with summary statistics*.   - Pregnancy prolongation (time from first antihypertensive dispensation to birth)* - Need for additional antihypertensive(s)* - Individual components of the primary composite outcome - Disease progression (new diagnosis of preeclampsia after randomization)   **Secondary Perinatal**  *Note: Variables denoted with a * are reported with treatment effect and 95% CI, all others are exploratory only and described with summary statistics*. *** Indicates core secondary outcome.*   - Preterm birth (<37; <34; <32; and <28 weeks’ gestation)** - Major congenital anomaly (as defined by EURO-CAT)* - Neonatal hypoglycemia* - Respiratory distress - Neonatal hypothermia - Individual components of primary composite outcome - Birthweight <10^th^ centile |

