**Developing a causal model using directed acyclic graphs (DAGs) to both identify and summarise causal pathways.**

1. Potential confounders will be determined by the above-named authorship team (a quorum of specialists with expert knowledge). All potential confounders are pre-exposure or at exposure.
   1. Covariates to be included in the selection model:
      1. Type of hypertension (gestational hypertension, chronic hypertension, preeclampsia)*
      2. Maternal diabetes mellitus (yes/no)*
      3. Plurality (1/2+)*
      4. Pre-existing renal disease
      5. Pre-existing autoimmune disease
      6. Maternal smoking during pregnancy
      7. Maternal body mass index
      8. IVF/ART conception
      9. Maternal socioeconomic status (SEIFA quintile)
      10. Maternal age at delivery
      11. Mode of birth (neonatal outcomes only)

*Variables denoted with * are included in the Giant PANDA randomization algorithm.*

**Causal pathway and confounding** (excerpt from Causal Inference, What if. M Hernan & J Robins p85: <https://www.hsph.harvard.edu/miguel-hernan/causal-inference-book/>)

*“...the bias has the same structure: it is due to the presence of a cause (known covariate L or unknown covariate U) that is shared by the treatment A and the outcome Y, which results in an open backdoor path between A and Y. We refer to the bias caused by shared causes of treatment and outcome as confounding…”*

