**Define treatment strategy (exposure), assignment procedures, and follow-up period.**

1. The target trial would randomize at the point of diagnosis of a hypertensive disorder of pregnancy (chronic hypertension, gestational hypertension, or preeclampsia). Women would be randomized in a 1:1 ratio to either labetalol or nifedipine. Follow-up would be until 28 days postpartum, and reasons for drop out would include non-adherence to medication, failure to provide consent, unplanned crossover of participants, and random loss to follow up.
2. In the emulated trial, women will be ‘randomized’ at the point of first dispensation of either labetalol or nifedipine at or beyond 11 weeks’ gestation. We will exclude women who were taking both medications prior to 11 weeks’ gestation (unable to be randomized). We will exclude hypertensive women who received neither labetalol or nifedipine (contraindication or non-indication; this cohort will be described). We will also exclude women without hypertension who received labetalol or nifedipine (this cohort will be described).

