**Outcome definitions – primary and secondary outcomes.**

1. In the target trial, the **primary maternal outcome** is severe hypertension (systolic blood pressure ≥160mmHg). We do not have reliable access to blood pressure measurements; however, our much larger sample size allows us to investigate downstream effects of severe hypertension (severe morbidity). Therefore, the primary maternal outcome will be a composite comprising:
   1. Maternal mortality (all cause) (yes/no)
   2. Eclampsia (yes/no)
   3. HELLP syndrome (yes/no)
   4. Stroke (yes/no)
   5. Cortical blindness (yes/no)
   6. Retinal detachment (yes/no)
   7. Pulmonary oedema (yes/no)
   8. Placental abruption (yes/no)
   9. Liver rupture (yes/no)
   10. Need for dialysis (yes/no)
   11. Need for extracorporeal membrane oxygenation (ECMO) (yes/no)
2. In the target trial, the **primary perinatal outcome** is a composite of stillbirth (≥20 weeks’ gestation), neonatal death (≤28 days post-birth), and neonatal unit admission requiring separation of the infant and mother. We will maintain this outcome by reporting a primary perinatal outcome comprising:
   1. Stillbirth ≥ 20 weeks’ gestation (yes/no)
   2. Neonatal death ≤ 28 days post-birth (yes/no)
   3. Severe neonatal morbidity, comprising:
      1. Neonatal seizures (yes/no)
      2. Necrotizing enterocolitis (yes/no)
      3. Hypoxic-ischemic encephalopathy (yes/no)
      4. Birthweight <3^rd^ centile (yes/no)
      5. Bacterial sepsis (yes/no)
      6. Intracranial hemorrhage (yes/no)
      7. Neonatal asphyxia
      8. Cardiac arrest (yes/no)
      9. Requirement for mechanical or non-mechanical resuscitation (yes/no)
      10. Requirement for intubation or mechanical ventilation (yes/no)
3. In the target trial, there were several **secondary maternal outcomes** (see *Target Trial Emulation* Table Sfor full list). As these secondary outcomes are largely accounted for in our primary composite outcome, we will report the following secondary outcomes with treatment effect and 95% confidence intervals (CI):
   1. Need for additional antihypertensives (yes/no)
   2. Progression from gestational hypertension to preeclampsia (yes/no)

Additionally, the following outcomes will also be reported in an exploratory capacity (i.e., with summary statistics only):

1. Individual components of the primary outcome (all reported as yes/no)
2. Hospital admission prior to 37 weeks’ gestation (yes/no)

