**PART THREE: SUBGROUP ANALYSES**

Subgroup analyses will be undertaken by:

- Type of hypertensive disorder (chronic hypertension, gestational hypertension, and preeclampsia).
- Per-protocol and complete case analyses.
- Timing of randomization (11+0 – 19+6; 20+0 – 27+6; 28+0 – 36+0).
- Timing of birth (≤34 weeks’ gestation; >34 weeks’ gestation).

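### Hypertension type is weighted on and used as a subgroup, but it is not dated to first dispensation, so some women may be classified by a diagnosis made after treatment began

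*SAP*

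**What the plan says.** Five parts of the SAP bear on this.

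- **Covariate.** The section on developing a causal model with DAGs lists "Type of hypertension (gestational hypertension, chronic hypertension, preeclampsia" first among the selection-model covariates and states: "All potential confounders are pre-exposure or at exposure". The balance tables under Details of primary analysis models show the variable in both primary models, with gestational hypertension as reference and chronic hypertension and preeclampsia as the other levels. The Part One table lists it as a maternal baseline characteristic.
- **Subgroup.** Part Three: "Type of hypertensive disorder (chronic hypertension, gestational hypertension, and preeclampsia".
- **Outcome.** The Target Trial Emulation table has "Disease progression (new diagnosis of preeclampsia after randomization", without an asterisk, so for summary statistics only. Outcome definitions has "Progression from gestational hypertension to preeclampsia (yes/no", among the outcomes to be given a treatment effect and 95% CI.
- **Eligibility.** Project Overview: "All women who gave birth in Victoria between 2009 – 2020 and whose pregnancies were affected by hypertensive disorders". Anticipated Sample Size and the definition of the source population likewise set no order between diagnosis and dispensation.
- **Time zero.** In the section on treatment strategy, "women will be ‘randomized’ at the point of first dispensation of either labetalol or nifedipine at or beyond 11 weeks’ gestation". A stratum starting treatment at 11+0 to 19+6 weeks is planned.

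**The concern.** A confounder must be fixed by time zero. Here a woman qualifies if a hypertensive disorder is diagnosed at any point in the pregnancy, while her clock starts at first dispensation. The three-level variable has no category for a woman not yet diagnosed, and nothing says how preeclampsia present at the start is told apart from preeclampsia that appears later.

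Three results are exposed. The average treatment effect for both primary outcomes could be over-adjusted, because progression to preeclampsia is a plausible route to eclampsia and HELLP syndrome in the maternal composite. The preeclampsia subgroup could be selected on a post-treatment event. The progression outcome restricted to gestational hypertension would be empty if that label is a final diagnosis, since women who keep it have by construction not progressed.

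**Working it through.** The SAP gives no figure to reproduce on this point. The check sets its statements side by side and then sizes the possible effect on assumed inputs.

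**Step 1: can the text classify a woman by a later event?**

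- Eligibility needs a hypertensive diagnosis in the pregnancy and a dispensation at 11+0 to 36+6 weeks, in no stated order.
- A woman dispensed before her only qualifying diagnosis is therefore eligible as written.
- She must receive one of three types, and that type can only come from a record made after exposure.
- The clearest case is a woman starting at 11+0 to 19+6 weeks and coded gestational hypertension or preeclampsia. This uses the usual definition of onset from 20 weeks, which the SAP does not state. Chronic hypertension can be known before then.
- The general statement that confounders precede or coincide with exposure does not close the gap. The same list contains "Mode of birth (neonatal outcomes only", which cannot precede exposure. That item is absent from the neonatal balance table, but its listing shows that the statement was not applied as a dating rule.

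**Step 2: how much preeclampsia imbalance is weighted away?**

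Standardised difference: d = (p1 − p0) / √{[p1(1 − p1) + p0(1 − p0)] / 2}. The prevalence p0 is not given, so it is varied.

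| Model | Raw d (SAP) | Weighted d (SAP) | p1 − p0 at p0 = 10% | p1 − p0 at p0 = 50% |
| --- | --- | --- | --- | --- |
| Maternal | 0.1222 | 0.0058 | 4.0 points | 6.1 points |
| Neonatal | 0.1419 | 0.0003 | 4.7 points | 7.1 points |

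Any part of this imbalance that arose before dispensation is confounding and should be removed. Any part that arose afterwards may be treatment effect. The SAP does not allow the two to be separated.

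**Step 3: worst case (all inputs assumed).** Composite risk is 8% with preeclampsia and 2% without. All preeclampsia is post-treatment, and the whole drug effect runs through it. Progression is 40% on labetalol and 32% or 36% on nifedipine.

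- Labetalol: 0.40 × 8% + 0.60 × 2% = 4.40%.
- Nifedipine at 32%: 0.32 × 8% + 0.68 × 2% = 3.92%, RR = 3.92 / 4.40 = 0.89.
- Nifedipine at 36%: 0.36 × 8% + 0.64 × 2% = 4.16%, RR = 4.16 / 4.40 = 0.95.
- Conditional on final type, risks are 8% v 8% and 2% v 2%, so RR = 1.00.

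**Step 4: a milder case (also assumed).** Half of the women already have preeclampsia at dispensation (risk 8%), and the other half behave as in step 3.

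- Labetalol: 0.5 × 8% + 0.5 × 4.40% = 6.20%.
- Nifedipine at 32%: 0.5 × 8% + 0.5 × 3.92% = 5.96%, RR = 5.96 / 6.20 = 0.96.

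Conditioning on final type would again give 1.00, but less effect is lost.

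**Step 5: can the sign change?** Assume unmeasured severity in 30%; preeclampsia risk on labetalol 20% (not severe) or 50% (severe); outcome risk 2%, plus 6 points with preeclampsia and 4 points with severity; no direct drug effect. Preeclampsia on labetalol is 0.7 × 20% + 0.3 × 50% = 29%, so outcome risk is 2 + 6 × 0.29 + 4 × 0.30 = 4.94%.

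| Drug multiplies preeclampsia risk by | Total effect | After adjusting for preeclampsia |
| --- | --- | --- |
| 0.8 (29% to 23.2%) | 4.592% v 4.94%, RR 0.93 | RR 1.01 |
| 1.25 (29% to 36.25%) | 5.375% v 4.94%, RR 1.09 | RR 0.98 |

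The adjusted values standardise to the pooled preeclampsia distribution at 90% labetalol and 10% nifedipine. The small reversal arises because, among women without preeclampsia, the share with severe disease differs by drug once the drug affects who progresses.

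**The case against.** Using type as a covariate and new preeclampsia as an outcome is not an error. The target trial has type in its randomization algorithm and new preeclampsia among its outcomes. The two uses are compatible if both are dated to time zero, and the emulation table already places new preeclampsia after it. This stands: the defect is the missing dating rule, not the dual use.

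A reader might infer that type was coded from the final diagnosis. The SAP never says so; that remains a risk it does not exclude. A reader might also infer that type is unknowable for everyone starting before 20 weeks. That fails for chronic hypertension, and the size and make-up of the early stratum are not given. Nor does the absence of type from the imputation table show late coding: women without hypertension are excluded, so every included woman has a type through eligibility.

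The RR of 1.00 in step 3 follows from its assumptions. Dispensation runs to 36+6 weeks, so some women may well have preeclampsia when they start. For them type is a genuine confounder, and dropping it would trade possible over-adjustment for confounding by severity.

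What the objection does not answer is the woman dispensed before diagnosis. The SAP admits her and gives her no baseline level.

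**Conclusion.** The point holds in this form: eligibility and type are not tied to first dispensation, so any woman dispensed before her qualifying diagnosis is classified by a post-exposure event, contrary to the SAP's own statement on confounder timing. To the extent this happens, the primary estimates lose drug effect that acts through progression to preeclampsia, and the preeclampsia subgroup is not a baseline subgroup. The progression outcome in Outcome definitions is empty only if gestational hypertension is a final diagnosis.

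The size cannot be read from the SAP. Full attenuation (0.89 to 0.95 becoming 1.00) is a worst case on assumed risks; preeclampsia already present at dispensation reduces the loss. The early-start example also depends on the usual 20-week definition. The emulation table and Outcome definitions separately disagree on who can progress and on whether a treatment effect with CI is reported. This is worth correcting, but it is not evidence that the reported balance or estimates are wrong.

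**What to change.** 1. Define type from diagnoses dated on or before first dispensation, with a separate level for women with no dated diagnosis by then. Use this variable in both primary models and in the subgroup analysis.
2. Count preeclampsia as progression only if first recorded after time zero in women free of it at time zero. Align the emulation table and Outcome definitions on the population and on whether an effect with CI is reported.
3. Where dates are unavailable, keep the current variable and add a sensitivity analysis of both primary outcomes using chronic hypertension yes/no. State that this may leave confounding by preeclampsia present at treatment start.
4. Do not call the preeclampsia subgroup a baseline subgroup unless it is dated.

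If type was already dated to dispensation, a sentence saying so, and how women not yet diagnosed were classified, settles items 1 and 4.

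The cost is otherwise the recoding of one variable and a rerun of the affected models; at B = 1000 and M = 2 that is 1000 × 2 = 2,000 completed datasets per analysis. An outcome defined as new preeclampsia after time zero already presupposes dated diagnoses, but the SAP does not say which linked records carry the dates. Detail will be lost where dates are missing or the diagnosis was made as an outpatient.

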**Handling of missing data**

Detailed description of the patterns of missing data will be provided. This will include the proportion of missingness for each analysis model covariate and those used in the construction of the minimization criteria. We will not impute missing exposure or outcome data. Mothers with missing exposure data (i.e., no record of prescription of either labetalol or nifedipine) will be excluded from analysis. The magnitude and characteristics of these mothers will be summarized in a supplementary table.

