**Details of imputation models**

|  | Observations per m | | | |
| --- | --- | --- | --- | --- |
| Variable | Complete | Incomplete | Imputed | Total |
| BMI | 7174 | 371 | 371 | 7545 |
| Smoking | 7471 | 74 | 74 | 7545 |
| SEIFA | 7542 | 3 | 3 | 7545 |
| IVF/ART Conception | 7521 | 24 | 24 | 7545 |
| Birthweight | 7532 | 13 | 13 | 7545 |

Observed raw data

| Variable | N | Mean | SD | Min | Max |
| --- | --- | --- | --- | --- | --- |
| BMI | 7174 | 31.71 | 7.50 | 10.01 | 59.88 |
| Smoking | 7471 | 0.16 | 0.37 | 0 | 1 |
| SEIFA | 7542 | 3.13 | 1.31 | 1 | 5 |
| IVF/ART Conception | 7521 | 0.09 | 0.28 | 0 | 1 |
| Birthweight | 7532 | 2926.36 | 734.23 | 160 | 5860 |

Imputed data bootstrap 1, m=1

| Variable | N | Mean | SD | Min | Max |
| --- | --- | --- | --- | --- | --- |
| BMI | 7545 | 31.69 | 7.49 | 10.01 | 59.88 |
| Smoking | 7545 | 0.16 | 0.37 | 0 | 1 |
| SEIFA | 7545 | 3.13 | 1.31 | 1 | 5 |
| IVF/ART Conception | 7545 | 0.09 | 0.28 | 0 | 1 |
| Birthweight | 7545 | 2922.03 | 741.39 | 160 | 5860 |

Imputed data bootstrap 2, m=2

| Variable | N | Mean | SD | Min | Max |
| --- | --- | --- | --- | --- | --- |
| BMI | 7545 | 31.69 | 7.51 | 10.01 | 59.88 |
| Smoking | 7545 | 0.17 | 0.37 | 0 | 1 |
| SEIFA | 7545 | 3.13 | 1.31 | 1 | 5 |
| IVF/ART Conception | 7545 | 0.09 | 0.28 | 0 | 1 |
| Birthweight | 7545 | 2922.11 | 741.21 | 160 | 5860 |

Proportions for SEIFA (m=1)

| **SEIFA Quintile** | **Observed** | **Imputed** | **Completed** |
| --- | --- | --- | --- |
| 1 | 0.154 | 0.333 | 0.154 |
| 2 | 0.163 | 0.333 | 0.163 |
| 3 | 0.266 | 0.000 | 0.265 |
| 4 | 0.237 | 0.000 | 0.237 |
| 5 | 0.180 | 0.333 | 0.180 |

Proportions for smoking status (m=1)

| **Smoking Status** | **Observed** | **Imputed** | **Completed** |
| --- | --- | --- | --- |
| Yes | 0.165 | 0.122 | 0.164 |
| No | 0.835 | 0.878 | 0.836 |

Proportions for IVF/ART conception (m=1)

| **IVF/ART Conception** | **Observed** | **Imputed** | **Completed** |
| --- | --- | --- | --- |
| Yes | 0.087 | 0.208 | 0.088 |
| No | 0.913 | 0.792 | 0.912 |

Proportions for BMI (m=1)

[figure not shown]

Proportions for birthweight (m=1)

[figure not shown]

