**Details of primary analysis models**

1) Maternal primary analysis model: Propensity score covariate balance assessment, pooled across all imputations and bootstraps

| **Variable** | **Standardised Differences** | |
| --- | --- | --- |
|  | **Raw** | **Weighted** |
| Hypertensive subtype |  |  |
| *Gestational hypertension (ref)* | – | – |
| *Chronic hypertension* | 0.0536 | 0.0046 |
| *Preeclampsia* | 0.1222 | 0.0058 |
| Maternal comorbidities |  |  |
| *No (Ref)* | – | – |
| *Yes* | 0.1745 | 0.0075 |
| Parity |  |  |
| *Multiparous (Ref)* | – | – |
| *Nulliparous* | 0.1103 | 0.0370 |
| Smoking in pregnancy |  |  |
| *No (Ref)* | – | – |
| *Yes* | 0.0062 | 0.0124 |
| Plurality |  |  |
| *Singleton (Ref)* | – | – |
| *Twins or higher order* | 0.0666 | -0.0051 |
| ART/IVF Conception |  |  |
| *No (Ref)* | – | – |
| *Yes* | 0.1759 | -0.0057 |
| SEIFA Quintile |  |  |
| *1 (Ref)* | – | – |
| *2* | -0.0095 | -0.0123 |
| *3* | -0.0933 | -0.0143 |
| *4* | 0.0299 | -0.0007 |
| *5* | 0.1331 | 0.0153 |
| Maternal age | 0.1623 | 0.0012 |
| Maternal body mass index | -0.0366 | 0.0193 |

Test of overidentifying restrictions: chi2(11) = 17.67

Prob > chi2 = 0.0894

Covariates are balanced.

1. Neonatal primary analysis model: Propensity score covariate balance assessment, pooled across all imputations and bootstraps

| **Variable** | **Standardised Differences** | |
| --- | --- | --- |
|  | **Raw** | **Weighted** |
| Hypertensive subtype |  |  |
| *Gestational hypertension (ref)* | – | – |
| *Chronic hypertension* | 0.0459 | 0.0053 |
| *Preeclampsia* | 0.1419 | 0.0003 |
| Maternal comorbidities |  |  |
| *No (Ref)* | – | – |
| *Yes* | 0.1675 | 0.0083 |
| Parity |  |  |
| *Multiparous (Ref)* | – | – |
| *Nulliparous* | 0.0940 | 0.0413 |
| Smoking in pregnancy |  |  |
| *No (Ref)* | – | – |
| *Yes* | 0.0081 | 0.0132 |
| Plurality |  |  |
| *Singleton (Ref)* | – | – |
| *Twins or higher order* | 0.0988 | -0.0101 |
| ART/IVF Conception |  |  |
| *No (Ref)* | – | – |
| *Yes* | 0.1889 | -0.0100 |
| SEIFA Quintile |  |  |
| *1 (Ref)* | – | – |
| *2* | -0.0174 | -0.0108 |
| *3* | -0.0936 | -0.0136 |
| *4* | 0.0289 | -0.0027 |
| *5* | 0.1465 | 0.0132 |
| Maternal age | 0.1702 | -0.0006 |
| Maternal body mass index | -0.0260 | 0.0155 |

Test of overidentifying restrictions: chi2(10) = 15.23

Prob > chi2 = 0.1236

Covariates are balanced.

1. Propensity score overlap plots for primary maternal and neonatal analyses, across all imputations (M=0, M=1, M=2)

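### The appended propensity models depart without explanation from the SAP's own covariate list, and balance is not shown for diabetes, renal disease and autoimmune disease separately

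*SAP*

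**What the plan says.** The SAP section *Developing a causal model using directed acyclic graphs* gives a definite list of 11 covariates for the selection model. Three of them are "Maternal diabetes mellitus (yes/no", "Pre-existing renal disease" and "Pre-existing autoimmune disease". Diabetes carries a star, meaning that it is part of the target trial's randomization algorithm. Parity is not on the list. Mode of birth is, for neonatal outcomes only, although the same section says that all potential confounders are measured before or at exposure.

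The section *(A) Selection model using inverse probability weights* adds that the exposure model includes the minimization variables. It says that balance will be assessed by standardized mean differences, variance estimates and propensity overlap. It does not mention an overidentification test.

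The appendix *Details of primary analysis models* shows what was fitted. Both balance tables have one No/Yes row under "Maternal comorbidities", include parity, and omit mode of birth. Below them stand "Test of overidentifying restrictions: chi2(11) = 17.67" (p = 0.0894) and "Test of overidentifying restrictions: chi2(10) = 15.23" (p = 0.1236), each followed by a statement that the covariates are balanced. No variance comparison is tabulated.

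On missing data, *Handling of missing data* states "We will not impute missing exposure or outcome data". The table in *Details of imputation models* has the row "Birthweight | 7532 | 13 | 13 | 7545", that is, 13 birthweights imputed. Birthweight below the 3rd centile is a component of the primary perinatal outcome.

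**The concern.** The causal reading of the results rests on exchangeability given the chosen covariates, as the SAP says under *Causal contrasts of interest*. A reader therefore needs to know which covariates were used and to see balance on each.

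Balance on having any comorbidity does not give balance on its parts. Suppose, for simplicity, that the three diseases do not overlap, with proportions d, r and a in an arm. The combined term balances d + r + a. A surplus of r in one arm offset by a deficit of d leaves that sum unchanged. If the diseases carry different outcome risks, confounding can remain behind a standardized difference near zero.

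This matters most for diabetes, which the SAP singles out as a randomization factor. Comorbidity is also among the larger raw imbalances: 0.1745 in the maternal table and 0.1675 in the neonatal one. The single statement that the covariates are balanced, placed directly under a test result, invites a reader to take the question as settled.

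**Working it through.** **1. Planned list against fitted terms.**

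| Covariate | Planned list | Maternal table | Neonatal table |
| --- | --- | --- | --- |
| Diabetes | separate | not separate | not separate |
| Renal disease | separate | not separate | not separate |
| Autoimmune disease | separate | not separate | not separate |
| Combined comorbidity term | no | yes | yes |
| Parity | no | yes | yes |
| Mode of birth | neonatal only | no | no |

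Hypertension subtype, plurality, smoking, BMI, ART, SEIFA and age agree. So 3 of the 10 planned maternal covariates, and 4 of the 11 planned neonatal ones, have no row of their own. The appendix does not define the combined term. That it merges the three diseases is inferred from the Part One descriptive table, which groups diabetes, autoimmune disease and renal disease under pre-existing comorbidities.

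**2. The stated test results.** The upper tail of the chi-square distribution at the stated degrees of freedom gives:
- Maternal: P(chi2 with 11 df > 17.67) = 0.0896, stated 0.0894.
- Neonatal: P(chi2 with 10 df > 15.23) = 0.1239, stated 0.1236.

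The agreement is within 0.0003. One degree of freedom either way gives 0.0608 or 0.1261 (maternal) and 0.0848 or 0.1722 (neonatal). The degrees of freedom are therefore not typing errors.

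**3. Terms per table.** Non-reference terms: subtype 2, comorbidity 1, parity 1, smoking 1, plurality 1, ART 1, SEIFA 4, age 1, BMI 1. The sum is 13, or 14 with a constant, and it is the same in both tables. Neither count matches 11 or 10. With SEIFA as one linear term the count would be 13 − 3 = 10, or 11 with a constant. That contradicts the separate quintile rows, and no single counting rule gives 11 for one table and 10 for the other when their term lists are identical.

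The planned maternal list has 14 terms: subtype 2, diabetes 1, plurality 1, renal 1, autoimmune 1, smoking 1, BMI 1, ART 1, SEIFA 4, age 1. With linear SEIFA it has 14 − 3 = 11. The maternal figure of 11 can thus be reached by more than one route, and the reader cannot tell which model was tested.

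**4. Balance that is shown.** The largest absolute weighted standardized differences are 0.0370 (maternal) and 0.0413 (neonatal), both for parity. The combined comorbidity term falls from 0.1745 to 0.0075 (maternal) and from 0.1675 to 0.0083 (neonatal).

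**5. Birthweight.** 13/7,545 = 0.17%. Birthweight is in neither balance table, so this is a question about the perinatal outcome only.

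**The case against.** The strongest reply is that balance does not depend on the overidentification test. The SAP planned standardized differences, and every tabulated one is at most 0.0413 after weighting. This stands for the terms shown. It does not reach the three diseases, which have no rows.

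A second reply is that only the propensity part is tabulated. The estimator is doubly robust, the outcome model takes its variables from the DAGs, and those figures cannot be seen here. Separate disease terms in the outcome model, or a DAG reason for parity, cannot be excluded. Nor can sparse data as the reason for merging, since about 10% of some 7,500 women (about 750) received nifedipine. This also stands, and it rules out saying that the diseases are unadjusted. It does not explain why the selection-model list and the fitted selection model differ. Adding parity, which precedes exposure, does no harm in itself; the list should simply say so.

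Three stronger readings are tempting.
- A reader might infer that the two tests were run on models different from those tabulated, or from each other. The tables are pooled over imputations and bootstraps, and the SAP does not say which dataset gave each chi-square or how its degrees of freedom were counted. The mismatch is unexplained, but it does not prove this.
- A reader might recompute the p-values at 13 degrees of freedom. That is not valid, because the statistic belongs to the test that was run and would change on refitting.
- A reader might infer that imputed birthweights entered the 3rd-centile component. The SAP allows auxiliary variables in the imputation model and does not say how these values were used.

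**Conclusion.** The point holds as a contradiction between the SAP's covariate list and its appended propensity models, with a gap in the evidence for balance. Three planned covariates have no balance shown separately, parity is used but unlisted, and mode of birth is listed but unused in the neonatal model. The last item is better resolved by changing the list, because mode of birth follows exposure and breaks the SAP's own rule for confounders.

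The balance tests cannot be linked to the 13 tabulated terms. Failing to reject at p = 0.0894 and p = 0.1236 does not demonstrate balance in any case.

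The size of any residual confounding cannot be stated: the document gives no arm-specific frequencies or risks for the three diseases. A reader might conclude that the groups are imbalanced or the primary estimates biased. The document does not support that, and what it does tabulate is reassuring.

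The conclusion assumes that the combined term stands for the three listed diseases. The birthweight conflict is real but small (0.17% of records) and has no bearing on exposure balance.

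**What to change.** - Enter diabetes, renal disease and autoimmune disease as separate terms in both the selection and the outcome models, and list the outcome-model terms in the appendix.
- Add parity to the covariate list, and remove mode of birth from it as post-exposure. Record both changes with reasons.
- Rerun the primary models and balance tables. For every term, report the standardized difference and the variance comparison that the selection-model section promised, and base the balance conclusion on these. The SAP sets no threshold, so one should be stated; an absolute standardized difference below 0.1 is a proposal.
- Correct the overidentification results, saying which dataset and terms they refer to and how the degrees of freedom were counted, or drop them. Remove the inference from a non-significant p-value to balance.
- Separately, build the 3rd-centile component from observed birthweight only, or state that imputed birthweight serves only as an auxiliary variable.

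The cost is a rerun of the bootstrap and imputation procedure for the primary analyses (B = 1000 with M = 2, so 1000 × 2 = 2,000 completed datasets), new balance tables and a few lines of text. No new data are needed.
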